## Abstract

**Background:**

Chronic neuropathic pain affects 69% of adults with spinal cord injury (SCI). Medication, as a primary treatment, has insufficient benefits and significant risks for addiction and adverse effects. Of the available mind and body approaches, Qigong is the most accessible for adults with SCI, with evidence for effectiveness in reducing pain. Still, there is insufficient evidence to make recommendations for adults with SCI. Thus, the feasibility of Qigong in SCI needs to be established. We previously demonstrated feasibility in a pilot study, in which 18 non-Hispanic White adults with SCI completed a 12-week remote Qigong program. However, three additional key elements need to be addressed before performing a larger effectiveness study: (1) feasibility and acceptability of Qigong in adults with SCI with health disparities, (2) feasibility of a study design with a control group, and (3) objective outcome measures.

**Objective:**

This National Center for Complementary and Integrative Health (NCCIH) R34 feasibility study—the HAPPINESS (Changing the Perceived Pain Intensity in Populations With Spinal Cord Injury and With Health Disparities) trial—will build upon our prior study to consolidate feasibility with a rigorous protocol. Our aims are (aim 1) to identify facilitators and barriers to participating in a Qigong study through community event meetings, focus groups, and interviews with 40 stakeholders, of whom at least 50% (n=20) have health disparities, and (aim 2) to establish the feasibility of study design and methods through prespecified targets for recruitment and enrollment, feasibility, and acceptability of design and outcomes.

**Methods:**

For aim 1, a total of 40 SCI stakeholders—adults with SCI, caregivers, health care professionals, or other stakeholders who have experience with caring for adults with SCI—will be invited to attend community event meetings, one focus group, or an interview, where they will provide input on facilitators and barriers related to participating in a Qigong study. For aim 2, using a phase I randomized controlled trial design, 40 adults with SCI-related neuropathic pain (with at least 50% [n=20] having health disparities) will be randomized to a 12-week remotely delivered Qigong intervention (practicing at least 3×/week with the Spring Forest Qigong’s “Five Element Qigong Healing Movements” video), or a short daily pain management survey, completed on a smartphone, iPad, or computer + 6-month follow-up. Feasibility benchmarks, as well as patient-reported outcome measures and objective data from the Fitbit Charge 6 watch, will be collected during the study.

**Results:**

The first participant was recruited on August 20, 2024. Study completion is estimated on January 31, 2027.

**Conclusions:**

The study results will facilitate a rigorous structure to design large effectiveness studies and facilitate a clear pathway for researchers to investigate Qigong and other mind and body approaches for whole-person health in adults with chronic or neurological disorders, including those with health disparities.

**Trial Registration:**

ClinicalTrials.gov NCT06140355; https://clinicaltrials.gov/study/NCT06140355

**International Registered Report Identifier (IRRID):**

DERR1-10.2196/82431

## Introduction

### Background

Chronic neuropathic pain impacts up to 69% of the 308,620 adults with spinal cord injury (SCI) [1-3]. This burning, electric, or stabbing pain can be debilitating and interfere with all aspects of life. The primary line of treatment is pain medication, but it often has insufficient benefits and carries uncomfortable side effects or risks for addiction [4,5]. In addition, there is an underrepresentation of minority groups, women, and older adults in SCI rehabilitation clinical trials [6]. For example, 14% of adults with traumatic SCI are of Hispanic origin; yet, there was an underrepresentation (<10%) of Hispanic or Latinx participants in SCI rehabilitation clinical trials in the United States between 2011 and 2020 [6].

Research showing the effectiveness of mind and body approaches for reducing pain in adults with SCI is limited to 7 studies, among which only 3 (on Yoga and Tai Chi) [7-9] looked at pain reduction, without mentioning which type of pain they were investigating [7-13]. One seated Tai Chi program was well-tolerated in adults with SCI (n=26) with reduced pain and a higher emotional and physical well-being after each session, but their weekly in-person group classes had a dropout of 60% [8].

We reported significant neuropathic pain reduction after remotely delivered Qigong in our feasibility pilot study of 18 adults with SCI-related neuropathic pain [14]. Sample sizes in the above-mentioned studies were small. Moreover, only our study [14] included adults with complete and incomplete tetraplegia, and Tsang et al [11] included adults with incomplete tetraplegia, but all others recruited adults with paraplegia only. Despite these promising results, more accessible interventions for adults with tetraplegia and larger studies are needed.

Substantial evidence suggests that mind and body treatments for physical and mental health may be particularly important for high-risk disadvantaged individuals, including racial or ethnic minorities and those with poor access to conventional treatments because of cost [15]. Factors such as offering the interventions in multiple languages, integrating feedback from participants, and designing programs that are compatible with cultural and religious beliefs would further improve the feasibility and acceptability of mind and body treatments and promote personal use [15-18]. Finally, since 2009, with the increasing opioid epidemic, the US military (Department of Defense [DoD] and Veterans Affairs) has made substantial efforts to provide multidisciplinary, holistic treatments to Veterans with chronic pain [19]. Mind and body approaches have helped military Service Members reduce their pain, improve function and self-management, and increase self-efficacy, but to what extent these approaches are used by adults with SCI to relieve neuropathic pain is unknown [19-22].

Of all mind and body treatment options, Qigong is the most accessible for adults with SCI due to the gentle movements, which can be done in standing, sitting, or lying positions, and due to its focus on breathing and body awareness [23-25]. Yet, there is insufficient evidence to make recommendations for Qigong for adults with SCI at this time. Thus, the feasibility of Qigong in SCI needs to be established. Remote delivery of Qigong is feasible for adults with SCI as it eliminates the commonly reported barriers of in-person interventions: fatigue, pain, transportation, and scheduling difficulties [26]. Moreover, our remotely delivered Qigong practice, which can be done standing, sitting, or lying down, aligns active movements to their ability level with kinesthetic imagery, that is, focusing on the feeling of moving the whole body as if in an upright position, because imagery may be an additional way to improve body awareness and reduce pain [14,25,27]. Therefore, adults with high-level tetraplegia after SCI can participate in this study because they can easily practice Qigong in their wheelchairs or lying down. In other studies, the minimum active muscle strength requirement for exercise programs often excludes these people.

Our preliminary data demonstrate the feasibility and acceptability of practicing Qigong for non-Hispanic White adults with SCI-related neuropathic pain with promising results in terms of pain relief, SCI-related symptoms, improved function, and mental well-being after Qigong practice [14,25]. Eighteen participants completed the study (18/21 enrolled; 86% retention), with 100% adherence to all study components, and 12 participants completed the 1-year follow-up. We enrolled a representative sample of women with SCI (6/18, 33%), adults 65+ years of age (7/18, 39%), living in rural areas (6/18, 33%), Veterans (3/18, 17%), adults in socioeconomic distress (12/18, 67%), and below the poverty threshold (3/18, 17%) [6,14,28]. Even though we recruited nationwide, all participants were non-Hispanic White, pointing to the need for more encompassing recruitment strategies. Participants practiced at home, at least 3 times per week for 12 weeks (123 minutes), with a Qigong video accessible via the internet (ie, the same video as proposed below). Our results showed feasibility and adherence to the intervention (138% of the required intensity of Qigong practice, representing 170 minutes) and no study-related adverse events.

However, despite these promising data, three additional key elements need to be addressed before performing a larger phase II effectiveness clinical trial: obtaining data from adults with SCI with health disparities on (1) feasibility and acceptability of participating in a Qigong study, (2) feasibility of the study design (including an active comparison group) and adherence to the interventions, and (3) obtaining objective outcome measures.

### Purpose of This Study

This R34 feasibility study—the HAPPINESS (Changing the Perceived Pain Intensity in Populations With Spinal Cord Injury and With Health Disparities) trial—will expand on our previous study to consolidate the feasibility with a rigorous protocol that addresses those key elements, with the aims listed below.

#### Aim 1: To Identify Facilitators and Barriers to Participating in a Qigong Study in Adults With SCI With Health Disparities

We will hold community event meetings, focus groups, and in-depth interviews with 40 stakeholders, including at least 50% with health disparities (ie, racial or ethnic minorities, Veterans, or living in rural, underserved areas), to identify which sociodemographic, behavioral, cultural, or structural factors facilitate or hinder participation in the study.

#### Aim 2: To Establish the Feasibility of the Study Design and Methods of the HAPPINESS Trial in 40 Adults With SCI (With at Least 50% [n=20] With Health Disparities) Through Prespecified Targets

The targets are as follows: (1) assessing recruitment and enrollment rates and identifying facilitators and barriers to participation; (2) evaluating recruitment rates for adults with complete versus incomplete SCI to determine the ratio of incomplete versus complete SCI for recruitment estimates in the next phase II randomized controlled effectiveness trial; (3) evaluating the feasibility and acceptability of the design by assessing adherence to Qigong practice or 2-minute daily pain management surveys, study satisfaction, and attrition rates in the Qigong and active comparison groups, as well as identifying facilitators and barriers to practicing Qigong at home; and (4) evaluating the feasibility of the data collection by assessing follow-up rates of outcome measures (% completed assessments at each time point, including objective measures, and weekly and monthly pain surveys).

This R34 feasibility study addresses the National Center for Complementary and Integrative Health (NCCIH) High Priority Pain Research (NOT-AT-22-007) using complementary and integrative interventions. The outcomes of this study will facilitate a rigorous structure to design large effectiveness studies and facilitate a clear pathway for researchers to investigate Qigong and other mind and body approaches for whole-person health, including in adults with chronic or neurological disorders, and those with health disparities.

## Methods

### Overall Study Design

For aim 1, we will hold community event meetings (ie, education and listening sessions) in town halls and health care settings for SCI stakeholders to share information about the research and hold listening sessions. We will organize focus groups and in-depth interviews using the Consolidated Framework for Implementation Research in the Twin Cities and in South Texas. We estimate we will have 3-5 attendees if on Zoom, and 5-8 attendees if in-person. We estimate holding 3 in-depth interviews with the most informative SCI stakeholders, to better understand the facilitators and barriers to remotely delivered Qigong practice, and identify which sociodemographic, behavioral, cultural, or structural factors facilitate or hinder participation in the study as a whole, including access to a computer, iPad, or smartphone and internet needed for Qigong practice or pain management through a Qualtrics survey, and remotely delivered questionnaires. If in person, the focus groups and interviews will be held in Minnesota (University of Minnesota–Twin Cities) and South Texas (University of Texas Rio Grande Valley [UTRGV]).

For aim 2, we will organize a feasibility phase I randomized controlled trial design where 40 adults with SCI-related neuropathic pain with at least 50% (n=20) with health disparities (racial or ethnic minorities, Veterans, or adults living in rural, underserved areas) are randomized to (experimental group) a Qigong introduction class and a 12-week remotely delivered Qigong intervention, with a 6-month follow-up, or (active comparison group) they complete daily 2-minute surveys to manage their pain sent through Qualtrics, with a 6-month follow-up.

Randomization will be generated by an independent biostatistician. The outcome assessors and the biostatistician on the study will be blinded to the group allocation. We have registered this clinical trial with the National Institutes of Health (NIH) clinical trials registry. Our feasibility pilot trial follows the guidelines according to the Obesity-Related Behavioral Intervention Trials model [29] and NCCIH [30]. Based on the guidelines, we developed aims, protocol, and the following a priori feasibility benchmarks to rigorously test the methodology and feasibility of the intervention before a larger effectiveness clinical trial is conducted.

Behavioral assessments will be acquired remotely at 3 time points: at baseline, after the 12-week interventions, and at the 6-month follow-up. This 6-month follow-up period will assess behavioral changes and the sustainability of Qigong practice adherence or pain management survey adherence in daily life. In our prior study, participants enjoyed continuing Qigong practice because it helped them manage their pain [14]. Both groups will receive weekly calls during the 12-week intervention period and monthly calls during the 6-month follow-up to assess neuropathic pain (primary outcome) and neuropathic pain medication, including opioid use, adherence to Qigong practice or the pain management surveys, adverse events, illnesses, and use of health care services. Qualitative information will be collected about their adherence, adverse outcomes, if any, perceptions, effects, and satisfaction with the Qigong practice or pain management surveys. Ecological momentary assessments (EMAs), consisting of 2-minute Qualtrics surveys are delivered 4 times per day for 3 weeks at baseline, during the last 3 weeks of the 12-week interventions, and during the last 3 weeks of the 6-month follow-up to identify feasibility of data that can explore causal relationships between variables of mood, activity, sleep, and so on, and neuropathic pain to understand in each individual which variables increase or decrease neuropathic pain. Objective data on sleep, stress, and other information will be collected continuously with the Fitbit Charge 6 wrist device. Fitbit data will also be time-synchronized with EMA data at those 3 time points to evaluate the feasibility of data that can explore causal relationships between physiological data, behavioral data, and neuropathic pain. The study is offered in English and Spanish to increase accessibility to those for whom English may be a barrier.

The SPIRIT (Standard Protocol Items: Recommendations for Interventional Trials) 2013 checklist with recommended items to address in a clinical trial protocol and related documents (Multimedia Appendix 1) and the SPIRIT template of recommended content for the schedule of enrollment, interventions, and assessments (Table 1) are included.

**Table 1 table1:** Scheduling of enrollment, intervention, and assessments.

		Study period			
Timepoint		Enrollment	12-week intervention	6-month follow-up	Close-out
**Enrollment**		Week 0	Week 1-12	Week 13-37	Week 38
	Eligibility screen	✓			
	Informed consent	✓			
	Baseline assessments (Zoom questionnaires)	✓			
	Allocation	✓			

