We will organize weekly (during the intervention) and monthly check-ins (during the 6-month follow-up) to encourage adherence. The Qigong group will also receive a 1:1 session per month with the Qigong instructor to verify the quality of practice and address any questions. The research staff will contact the participant if the pain management surveys are not completed 2 days in a row.

All participants will continue their prescribed or over-the-counter pain medication and maintain their regular standard-of-care health care appointments. However, any current regular (3 times per week or more) mind and body practices, such as Tai Chi, Qigong, or any rehabilitation programs that would influence outcomes, will not be permitted.

The study does not provide compensation for research-related injuries or unexpected urgent care.

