#### Feasibility Benchmarks

Our feasibility markers are consistent with models and guidelines for intervention development (Table 2) [29,42]. Based on prior publications [43-46], we will assess the following a priori feasibility markers.

**Table 2 table2:** Feasibility benchmarks.

	Feasibility item and details	Benchmark (go/no-go criteria)
Recruitment and enrollment	Assess recruitment rates (screens and enrollment per trimester, sex, and racial outcomes). Evaluate the recruitment rate for complete and incomplete SCI^a^. We aim to recruit 40 participants between mid-year 1 and year 2.	The proportion of potential participants contacted who agreed to participate: 80% is excellent and 70% good. Ratio of complete/incomplete SCI. We estimate recruitment of 30%-40% of adults with complete, 60%-70% with incomplete SCI. Reasons for (not) participating and information collected during focus groups or interviews will help delineate facilitators and barriers to participation, including computer or internet access.
Feasibility and acceptability of the study design	Attrition rates in the Qigong or pain management survey groups.	Proportion of people withdrawing from the interventions. Dropout due to unrelated reasons will count as part of the general attrition. A proportion of 90% is excellent, and 80% good.
Feasibility, adherence, and acceptability of the Qigong practice	Assess intervention adherence, average Qigong practice, at least 3×/week (123 minutes), pain management surveys (daily), and satisfaction with the Qigong practice or pain management surveys. Identify facilitators and barriers to practicing Qigong at home or completing the pain management surveys.	Weekly and monthly check-ins (reporting minutes/week of practice) to identify facilitators and barriers to pain management surveys or practicing Qigong. The Qualtrics website (for pain management surveys) or Spring Forest Qigong website (for Qigong practice) logs time and duration of video access. A Spring Forest Qigong-certified instructor will do a 1:1 Qigong session with each participant via Zoom monthly for quality control and to give guidance. Feasibility: Excellent: >80% participants practice at least 2×/week; good ≥70%. For the pain management survey: completion of surveys at least 5 out of 7 days. Dropout due to lack of interest will be counted as general attrition: 10% dropout is excellent, 20% is good.

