#### Primary Clinical Endpoints

We will use the patient-reported outcome measures of pain intensity PainDETECT [50] and the Numeric Pain Rating Scale [31] for the highest, average (ie, pain experienced most of the time), and lowest pain intensity in the prior week. The Numeric Pain Rating Scale [31] and PainDETECT [50] will be assessed weekly during the Qigong or pain management survey intervention period and then monthly during the 6-month follow-up period.

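### The unlimited claim of blinded outcome assessors cannot hold for the primary pain ratings taken in the weekly and monthly adherence calls

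*Protocol article*

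**What the plan says.** In the protocol article, Overall Study Design says of blinding: "The outcome assessors and the biostatistician on the study will be blinded to the group allocation". No outcome, visit or mode of collection is exempted.

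The same section describes the calls: "Both groups will receive weekly calls during the 12-week intervention period and monthly calls during the 6-month follow-up to assess neuropathic pain (primary outcome"). The sentence goes on to list "adherence to Qigong practice or the pain management surveys, adverse events, illnesses, and use of health care services". The next sentence adds qualitative information on "perceptions, effects, and satisfaction with the Qigong practice or pain management surveys".

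Three other places describe the same contacts:
- Interventions gives their purpose: "We will organize weekly (during the intervention) and monthly check-ins (during the 6-month follow-up) to encourage adherence".
- Feasibility Benchmarks (Table 2) gives a further use: "Weekly and monthly check-ins (reporting minutes/week of practice) to identify facilitators and barriers to pain management surveys or practicing Qigong". Its safety row treats check-in and call as one contact.
- Primary Clinical Endpoints names the Numeric Pain Rating Scale and PainDETECT, which "will be assessed weekly during the Qigong or pain management survey intervention period and then monthly during the 6-month follow-up period".

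Ethical Considerations says that answers given in the weekly and monthly phone calls are entered in REDCap.

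**The concern.** The adherence questions differ by arm: minutes of Qigong practice in one, completion of a daily survey in the other. A caller cannot ask about them, or encourage the participant, without knowing which arm the participant is in. If that caller also takes the pain rating, the primary clinical endpoint is collected by an unblinded person, and the blinding statement is wrong for the outcome where a reader would most expect it to apply.

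Two things are at stake. A results paper that repeats the statement would describe the primary pain data as assessor-blinded when they were not. Also, Sample Size Calculation and Data Analysis say that the pain mean and SD, and the changes over time by group, will be used to size future studies. A spoken rating given to someone who knows the arm and promotes adherence is open to interviewer influence, and any such influence would pass into those mean changes unmarked.

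**Working it through.** No formula beyond a count applies, and the plan gives no figure to reproduce. The check sets the statements side by side.

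1. **Scope of the claim.** The blinding sentence in Overall Study Design covers outcome assessors in general. Nothing in the article narrows it.
2. **Where primary pain is collected.** Overall Study Design names neuropathic pain as the primary outcome of the calls. Primary Clinical Endpoints puts the two instruments on the same weekly-then-monthly schedule. The schedules match, and Ethical Considerations confirms that call responses become data.
3. **What else the call contains.** The sentence that assigns pain to the calls also assigns adherence to the named intervention: "to assess neuropathic pain (primary outcome) and neuropathic pain medication, including opioid use, adherence to Qigong practice or the pain management surveys". Table 2 adds practice minutes, and Interventions adds encouragement.
4. **Whether the call is divided.** The article describes no separate blinded rater for pain, and no split of the call into a blinded and an unblinded part.
5. **Inference.** The person who conducts a call as described must know or learn the arm, at the latest during the first call. That person also takes the pain rating. From then on the blinding statement and the description of the calls cannot both be true.
6. **Count.** 12 weekly calls + 6 monthly calls = 18 scheduled call-based ratings per participant.
7. **What is left outside the contradiction.** Table 1 lists Zoom questionnaires at enrolment, in the intervention period and at close-out. Secondary Clinical Endpoints puts all secondary outcomes at baseline, after the intervention and at 6 months. Under Impact and Type of Pain, these include PainDETECT again and the average pain intensity in the International SCI Pain Basic Data Set. Staff who make no calls could give these questionnaires blind. A statistician can work on coded arms. Ecological momentary assessment surveys reach participants by text or email, with no interviewer.
8. **Where a bias would act.** The benchmarks in Table 2 concern recruitment, attrition, adherence, completeness, satisfaction and safety. None uses a pain score. Pain is summarised descriptively, with no power calculation and no efficacy test stated. A uniform shift in the ratings would move the mean and leave the SD unchanged. The exposed quantity is therefore chiefly the mean pain change by group.

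**The case against.** The strongest reply is that an article condenses a fuller protocol. It does not say who makes the calls, and staff roles and call scripts are commonly left to that fuller document. Aim 2 also mentions weekly and monthly pain surveys, which leaves the mode of collection a little less certain. This stands as a caution, but it does not remove the contradiction. The article does not merely omit a split; it assigns pain and adherence to the same calls. If a separate blinded rater exists, the description of the calls needs correcting instead. If ratings are in fact self-entered, there is no assessor to blind.

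Other replies stand and limit the point:
- Participants know what they are doing, so blinding the caller would remove only part of any bias in a self-reported score.
- This is a feasibility study. No go/no-go benchmark depends on pain, and no test result could be a false positive.
- With 36 of 40 participants recruited by September 2025 (Results), changing how the primary outcome is collected would mix modes within and between participants.

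A reader might go further and infer that the calls bias pain in favour of Qigong, or that the next trial would be undersized by some multiple. The document supports neither. Both groups receive the calls and both are encouraged, so caller effects could partly cancel. The order of questions within a call is not given, and the list of topics puts pain first. No bias figure is given, and the article does not say that the next trial will be powered on the observed effect. Nor is every post-baseline pain measurement compromised, because PainDETECT is also listed among the outcomes assessed at the three time points.

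**Conclusion.** As written, the blinding statement is wrong for the call-based primary pain ratings: 18 scheduled per participant, from 12 weekly and 6 monthly calls. It can hold at most for the Zoom questionnaires at the three time points, provided that staff who do not make the calls give them, and for the biostatistician.

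This rests on two readings of the text: that calls and check-ins are the same contact, as Table 2 indicates, and that one person conducts the whole call, since no division is described. The size and direction of any bias cannot be derived. The consequence is a methods statement that claims too much and mean pain changes by group that must be carried forward as unblinded data. The feasibility conclusions are not affected.

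**What to change.** - **Correct the statement.** Limit the blinding claim to the Zoom questionnaires, if given by staff who do not make the calls, and to the statistician working on coded arms. State that pain ratings taken in the weekly and monthly calls are not assessor-blinded, and report them as such in the results and when planning the next trial.
- **Record the source.** For each pain rating, store who took it and by what mode.
- **Order the remaining calls.** Take the pain ratings before any discussion of adherence. This reduces prompting within the call but does not restore blinding, since a caller who has spoken to the participant before already knows the arm.
- **Optional.** Self-entry of the ratings before the call suits the next trial. It could be used for remaining contacts here only if the change of mode is flagged in the data.

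The first three steps cost a less favourable methods statement and a little extra recording. Self-entry costs more. It needs ethics approval as an amendment and versions in English and Spanish, and it may be harder for participants with high-level tetraplegia. It would also give the Qigong arm a regular pain survey resembling the comparator. It should not be treated as a small change at this stage.
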